### Health economic analysis

A separate health economic analysis plan will be written in accordance with best practice for economic evaluations alongside a clinical trial. We will conduct a within-trial cost–utility analysis following the intention-to-treat principle and consider two perspectives: (1) NHS and Personal Social Services (NHS&PSS) and (2) societal (incorporating NHS&PSS and wider costs). The primary outcome measure of the economic evaluation will be incremental cost per QALY. The EQ-5D-5L and ReQoL collected at baseline, 8 weeks and 26 weeks will provide the utility values for the calculation of QALYs. We will estimate the costs of providing gameChange using a micro-costing approach. We will consider and measure costs such as training, travel, therapy delivery time, supervision time, hardware, software licence, maintenance, assistance from technical support staff as well as additional consumables and capital expenditures required. An adapted version of the CSRI^7 14^ will be used to collect data on healthcare and social care use, impact on work, criminal justice services and informal care received. Furthermore, information on admissions to mental health inpatient wards and medication prescribed will be obtained by reviewing medical records.

We will report descriptive statistics for resource use, costs and health utilities at each follow-up time point. Differences between arms will be estimated using multi-level mixed effects linear regression models to allow for multiple follow-ups clustered by participant.

We will follow best practice methods for addressing missing data in cost-effectiveness studies. The joint uncertainty around incremental total costs and QALYs will be estimated using seemingly unrelated regression and decision uncertainty will be represented using a cost-effectiveness plane.

### Power calculation

The number of participants is based on the means and SDs observed in our original trial. We assume an average cluster size of five participants per therapist and an ICC of 0.01. We calculate power both for the clinical outcome (agoraphobic avoidance) and quality of life.

O-AS-Avoidance: Based on a sample size of 200 and end of treatment means of 3.6 (SD=2.8) in the intervention group and 5.3 (SD=2.2) in the control group, we would have 90% power to detect a difference (5% significance). At 6 months, with means of 3.2 (SD=3.1) in the intervention group and 5.4 (SD=2.1) in the control group, we would have 99% power to detect a difference.

ReQol: Based on a sample size of 200 and end of treatment means of 37.5 (SD=18.7) in the intervention group and 30.6 (SD=13.2) in the control group, we would have 84% power to detect a difference (5% significance). At 6 months, with means of 38.1 (SD=18.0) in the intervention group and 31.3 (SD=12.5) in the control group, we would have 86% power to detect a difference.

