**Methods and analysis:**

200 patients with psychosis and severe agoraphobic avoidance will be randomised (1:1) to receive gameChange in addition to treatment as usual (TAU) or to a waitlist control group receiving TAU. Assessments will be conducted blind to group allocation at baseline, 8 weeks (end of treatment) and 26 weeks (follow-up). The trial will be embedded in services in at least seven National Health Service (NHS) trusts across England. The primary outcome is agoraphobic avoidance at 26 weeks assessed with the Oxford Agoraphobic Avoidance Scale. The secondary clinical outcomes are agoraphobic distress, paranoia and social contacts. There will be tests of moderation of the main clinical outcome. Treatment acceptability, adverse effects and cost-effectiveness will also be assessed. The target estimand is the treatment policy estimand and all primary and secondary analyses will be carried out incorporating data from all participants including those who do not complete treatment.

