**Trial registration number:**

ISRCTN79060696.

Strengths and limitations of this studyA strength of this randomised controlled trial of gameChange virtual reality is that it is designed to collect information across multiple domains: clinical efficacy, level of engagement and adherence, healthcare resource use, adverse effects, health-related quality of life and generalisability.To enhance the generalisability of the results, the trial will be embedded in multiple psychosis services across the country.The trial will not be able to determine the components of gameChange that lead to clinical benefits.The trial is only powered to detect moderate improvements with treatment in agoraphobic avoidance.

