### Analysis

A full statistical analysis plan will be approved before any analysis. We will report data in line with the CONSORT 2018–SPI^16^ and 2025 statements^17^ showing attrition rates and loss to follow-up. All outcome analyses will be conducted by statisticians at Oxford’s Primary Care Clinical Trials Unit. The target estimand is the treatment policy estimand and all primary and secondary analyses will be carried out incorporating data from all participants including those who do not complete treatment. Every effort will be made to follow up all participants in both arms for research assessments.

Treatment effects on primary and secondary outcomes will be estimated using linear mixed effect models fitted to outcome variables at both main follow-up points (8 and 26 weeks). Fixed effects will be site, baseline assessment for the outcome under investigation, treatment, time and time*treatment interactions. Participants will be included as a random intercept to account for repeated measures and nested within therapist to account for clustering by staff deliverer. Treatment effects will be estimated for the primary outcome at each time point and reported separately as adjusted mean differences in scores between the groups with 95% CIs and two-sided p values. We will also calculate an effect size (Cohen’s d), which will be the between group treatment difference divided by the shared SD at baseline.

We will check for differential predictors of missing outcomes by comparing responders to non-responders on key baseline variables. Any significant predictors will be included in the analysis models in a sensitivity analysis. This accounts for missing outcome data under a missing at random assumption, conditional on the covariates included in the model. As a sensitivity analysis, we will assess whether treatment adherence is associated with missing data, and if it is associated, use inverse probability weights or multiple imputation to compare results.

To test the moderation hypotheses, we will extend the analysis model to include as fixed effects the putative moderator and its interaction with treatment; the coefficient of the interaction tests whether there is a differential treatment effect across levels of the moderator variable.

Collection of 34-week data for the control group will provide further information for secondary trial reports on, for example, treatment uptake, satisfaction, acceptability, adverse effects and outcomes.

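### The 90% power stated for O-AS avoidance at 8 weeks does not follow from its own inputs, which give about 99.7% with 200 patients

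*Protocol article*

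**What the plan says.** The Power calculation section takes its means and SDs from the earlier trial and assumes an average of five participants per therapist with an ICC of 0.01. For O-AS avoidance, with 200 patients and 5% significance, it states: "end of treatment means of 3.6 (SD=2.8) in the intervention group and 5.3 (SD=2.2) in the control group, we would have 90% power". For 6 months, with means of 3.2 (SD 3.1) and 5.4 (SD 2.1), it says "we would have 99% power to detect a difference". For ReQoL it gives 84% at end of treatment and 86% at 6 months, again for 200 patients. No attrition allowance appears in the section.

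Two further inputs stand elsewhere. The Abstract says that patients "will be randomised (1:1) to receive gameChange in addition to treatment as usual (TAU"), so there are 100 per arm. The Analysis section plans "adjusted mean differences in scores between the groups with 95% CIs and two-sided p values", so the test is two-sided. The box on strengths and limitations adds: "The trial is only powered to detect moderate improvements with treatment in agoraphobic avoidance".

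**The concern.** All the inputs to the 8-week O-AS power are printed, and so is the result, so the figure can be checked directly. A difference of 1.7 points on an SD of about 2.5 is roughly two thirds of an SD. With 100 per arm, power should then be close to its ceiling and not 90%.

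O-AS avoidance is the primary measure, and the Analysis section reports its treatment effect at 8 weeks as well as at 26. A reader who takes 90% at face value would see a modest margin at 8 weeks. On the stated inputs, about half the sample would already give that power. If instead the 90% reflects an input that is not printed, that input should bear on the other three power figures too, and the reader cannot tell whether it was applied to them.

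**Working it through.** **Inputs** (Power calculation section unless noted)
- 200 patients, 1:1 (Abstract): n = 100 per arm.
- Alpha 0.05, two-sided (Analysis section).
- Cluster size 5, ICC 0.01: design effect = 1 + (5 − 1) × 0.01 = 1.04.
- O-AS, 8 weeks: 3.6 (2.8) v 5.3 (2.2), difference 1.7.
- O-AS, 26 weeks: 3.2 (3.1) v 5.4 (2.1), difference 2.2.
- ReQoL: 37.5 (18.7) v 30.6 (13.2), difference 6.9; then 38.1 (18.0) v 31.3 (12.5), difference 6.8.

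**Formulas**
- SE = √[(s₁² + s₂²) × 1.04 / n].
- Power ≈ Φ(difference / SE − 1.96). This was checked with a noncentral t that allows unequal variances.

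**Check of the method on ReQoL**
- End of treatment: SE = √[(349.69 + 174.24) × 1.04 / 100] = 2.334; 6.9 / 2.334 = 2.956; power 84.0% (noncentral t 83.6%). Stated: 84%.
- 6 months: SE = √[(324.00 + 156.25) × 1.04 / 100] = 2.235; 6.8 / 2.235 = 3.043; power 86.1% (noncentral t 85.7%). Stated: 86%.

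Both reproduce at 100 per arm.

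**O-AS at 8 weeks**
- s₁² + s₂² = 7.84 + 4.84 = 12.68. Root-mean-square SD = √6.34 = 2.518, so d = 1.7 / 2.518 = 0.675.
- SE = √(12.68 × 1.04 / 100) = 0.363; 1.7 / 0.363 = 4.68; power = Φ(4.68 − 1.96) = Φ(2.72) = 99.7% (noncentral t 99.65%). Stated: 90%. Not reproduced.
- With 49 per arm: SE = √(12.68 × 1.04 / 49) = 0.519; ratio 3.28; noncentral t power 90.0%.

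**O-AS at 26 weeks**
- s₁² + s₂² = 9.61 + 4.41 = 14.02. SD = √7.01 = 2.648, so d = 2.2 / 2.648 = 0.831.
- SE = √(14.02 × 1.04 / 100) = 0.382; 2.2 / 0.382 = 5.76; power 99.99%. Stated: 99%.

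**Could another reading give 90% at 8 weeks with 200 patients?**

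| Variant | 8-week O-AS power |
|---|---|
| Design effect in the intervention arm only | 99.7% |
| Degrees of freedom from the number of clusters | 99.3% to 99.5% |
| Larger SD (2.8) in both arms | 98.7% |
| 20% loss, 80 per arm (assumed; not in the document) | 98.6% |
| Alpha 0.001 | 90.7% |
| ICC 0.25 to 0.30 in both arms | about 92% to 89% |

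A one-sided test would only raise power. The last two rows come near 90% but contradict the printed 5% and 0.01. They would also cut ReQoL power well below the stated figures: to about 35% and 38% with alpha 0.001, and to between 52% and 59% with an ICC of 0.25 to 0.30.

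**The case against.** The strongest case on the other side is that little depends on this figure. It understates power, it is not at the primary time point, and no design or analysis decision changes when it is corrected. All of that stands and limits the severity. It does not make the figure right.

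A reader might also infer three stronger points, and the documents support none of them.

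- **That the power of the primary analysis is wrong.** The primary time point is 26 weeks. There, 99% stated against 99.99% computed differs by about one point, and 99% is a natural way to print a value at the ceiling.
- **That the limitation about moderate improvements contradicts the power section.** The Introduction itself calls effects of 0.4 and 0.5 moderate and 0.8 large. With 200 patients the trial detects about d = 0.40 to 0.47 at 26 weeks with 80% to 90% power, which is moderate in the document's own terms. The d of 0.68 and 0.83 implied by the power inputs are effects carried over from the earlier trial, which is a different quantity from what the trial can detect.
- **That the O-AS and ReQoL figures were computed for different sample sizes.** This is conjecture. Both are labelled as resting on 200 patients, and no single smaller number gives both O-AS figures: 49 per arm gives 90.0% and 97.9%, and 57 per arm gives 93.8% and 99.1%. Alpha 0.001 with 200 patients comes close to both, so a smaller sample is not the only candidate.

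**Conclusion.** One printed figure is wrong on its own inputs. The 8-week O-AS power is about 99.7% and not 90%, a gap of almost 10 percentage points. This rests on 100 per arm with complete data, a two-sided 5% test, the stated means and SDs, and a design effect of 1.04; applying the design effect to one arm or both makes no practical difference. The source of the discrepancy cannot be determined from the document. Attrition alone would have to remove about half of each arm (100 to 49) to explain it. The 26-week figure, the two ReQoL figures and the sample size of 200 are not called into question. Severity is minor.

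**What to change.** Correct the 8-week O-AS power to about 99.7%, or print it as >99%. If 90% was intended, state the input that yields it (for example attrition, another ICC or another alpha) and apply it to all four power figures. The 26-week figure could also be printed as >99%.

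As an option, add the 26-week difference that 200 patients can detect with 90% power: about 1.24 points with complete data (1.24 / 2.648 = d of about 0.47), or about 1.39 points if 20% loss is assumed. The 20% is an assumption that the document does not give.

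The cost is a text correction. The sample size does not change.

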## Ethics and dissemination

The trial has received Health Research Authority and Health and Care Research Wales (HCRW) approval (IRAS 351247). The trial received ethical approval from the HCRW Wales Research Ethics Committee 3 (25/WA/0081). The trial has not yet started recruiting participants. Recruitment is planned to start in July 2025, and for the trial to be completed by February 2028. Any changes to the trial protocol will have sponsor and ethical approvals. The results of the trial will be published in a peer-reviewed journal and made open access. Deidentified participant data will be available in anonymised form on reasonable request, subject to review and contract with the University of Oxford, following the publication of results.

### Patient and public involvement

The trial team has an individual with lived experience leading patient and public involvement. Two patient advisory group meetings, involving nine patients across the country, were held to discuss this evidence generation plan. There has also been considerable lived experience contributions to the development of the VR intervention. 53 people with lived experience contributed over 500 hours’ worth of input into the development of gameChange.^18 19^ The new trial is supported by a LEAP, who will meet regularly during the project.
